**d) Primary Endpoints**

**Safety and Tolerability**:

- Severe local reactogenicity events (pain, tenderness, erythema/skin discoloration, edema, damage [vesiculation/ulceration], induration, formation of a crust or scab.
- Severe systemic reactogenicity events (fever, chills, headache, nausea, vomiting, malaise, myalgia, arthralgia, rash).
- Severe other adverse events (including laboratory abnormalities).
- All Serious Adverse Events.
- Proportion of volunteers with mild and moderate local and systemic reactogenicity events.
- Electroporation Tolerability Assessment Questionnaire Responses (Appendix B)

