5. The application of electroporation will result in a brief, localized muscle contraction at the site of administration, which may be painful. Approximately 10% of subjects may experience a tingling sensation in their arm and fingers after administration. Since intramuscular DNA delivery with electroporation results in increased intracellular uptake of plasmid at the site of injection and electric field application, the procedure may increase the frequency and/or severity of local site reactions. Such symptoms should not last longer than several days. However, volunteers will be removed from the study if injection reactions ≥ Grade 3 in severity occur
6. We do not know what effect the vaccine would have on an unborn child if given to a pregnant woman. Females of childbearing potential will be advised to use a reliable form of contraception, as discussed with a nurse counselor, until study completion. A pregnancy test will be performed at screening, on the day of vaccination, and at every visit throughout the course of the fourteen-month study. Males who are not anatomically sterile (those who have had a vasectomy or medically proven to be sterile)should use condoms until study completion to avoid pregnancy in a spouse or partner
7. Following vaccination a participant may become HIV positive on a routine HIV test. This test result does not mean that person has HIV or AIDS. It could mean that exposure to the vaccine resulted in the production of antibodies to it. In case of a positive HIV test result, an independent laboratory will confirm whether the positive test is the result of the vaccination or whether the participant contracted HIV through exposure in the community. In the event that an individual has a vaccine-induced positive serology, ADARC will provide documentation of that individual’s participation in this vaccine trial
8. It is unknown whether receiving this HIV vaccine will alter the immune response to any future HIV vaccine that may be developed in the future
9. The possibility of integration of the DNA plasmid vector into genomic DNA of transfected myocytes has been considered. Plasmid integration at a sufficiently high frequency carries the possibility of inducing deleterious gene expression modifying mutations (e.g. inactivation of a tumor suppressor gene). Potential side effects could include an increased risk of malignancy arising from the cells harboring the mutation(s).

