No more than one volunteer per day will be enrolled for the first four volunteers to receive electroporation in each dose group. For these four volunteers, an additional telephone call to assess safety and adverse events will be made on the day following vaccination. If four vaccinations by electroporation have occurred without greater than moderate adverse events, the remainder of the group can be enrolled with no fixed interval between volunteers.

A. **Description of Adverse Events (AE) Detection and Reporting:**

**i. Adverse Event Definition**: An adverse event is any noxious, pathologic, or unintended change in anatomical, physiologic, or metabolic functions, as indicated by physical signs, symptoms, and/or laboratory changes occurring in any phase of the clinical trial, whether associated with drug and whether or not considered drug related. All of the following are to be considered adverse events:

- An exacerbation of a pre-existing condition.
- An inter-current illness.
- Any drug interaction.
- Any event related to a concomitant medication.
- Development of an abnormal laboratory value or a significant change from baseline in a laboratory value within the range of normal, considered by the investigator to be clinically important.

Any adverse event prior to the first vaccination will be reported as a pre-existing condition on the “previous conditions” source document. At each outpatient visit, subjects will be questioned and/or examined by the PI or his designee for evidence of AEs. The onset and end dates, severity and relationship to study vaccine and EP device will be recorded in the medical record for each event.

**ii. Assessment of Severity:** The severity of the AE will be assessed according to the Adverse Event Severity Assessment Table (see Appendix C).

**iii. Serious Adverse Event (SAE) Definition:** An SAE is an AE that results in any of the following outcomes.

- Death
- Life threatening condition
- Hospitalization or prolongation of stay
- Persistent or significant disability or incapacity
- Congenital anomaly or birth defect
- Medically significant event, including laboratory abnormalities

Important medical events that do not result in death, are life threatening, or require hospitalization, may be considered SAEs when, based on appropriate medical judgment, they may jeopardize the volunteer, or may require medical/surgical intervention to prevent one of the outcomes listed in this definition.

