A life threatening event means an immediate risk of death from the event as it occurred. Life threatening does not include an event that, had it occurred in a more serious form, might have caused death. For example; drug-induced hepatitis that resolved without evidence of hepatic failure would not be considered life threatening even though drug-induced hepatitis can be fatal.

Any serious adverse event (SAE) and unexpected adverse event involving human subjects of an IRB-RU approved protocol will be reported to the Rockefeller University IRB within two (2) working days of the discovery. These events includes serious adverse events that occur anytime while enrolled in the study or within 30 days after a subject completed the study if reported spontaneously to the study team. The date of study completion for any subject is defined as either 30 days following the last study visit or the date a participant and/or Investigator determines that the participant can no longer comply with the requirements for any further study visits and evaluations, (e.g., the participant is prematurely discontinued from the study). In addition to the adverse event reports to Rockefeller, these reports should be appropriately reported to FDA in compliance with 21 CFR 312.32.

B. **Unanticipated Adverse Event Reporting:** Other adverse events that require written reporting to the IRB-RU within five (5) working days of the discovery include: [1] Any unanticipated problems or deviations from protocol conduct involving or creating more than minimal risk to subjects or others, or irregularities in the process of informed consent; [2] Physical or emotional harm to the subject during the execution of the experimental protocol; [3] A breach of confidentiality or privacy and; [4] Unexpected harmful effects of an investigational or FDA-approved drug, biologic or device, observed in other research setting similar to that of the approved project.

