### Indications for discontinuation of vaccinations in all volunteers:

If 3 or more of the volunteers participating in this trial develop an SAE or severe AE judged as definitely, probably or possibly related to the vaccine, and clinically significant by the Principal Investigator or designee, IAVI will request a review by the DSMB and the trial will be suspended pending a review of all safety data by the DSMB. The study treatment may be unblinded at the discretion of the DSMB. Following this review, the DSMB will make a recommendation to the Principal Investigator and IAVI regarding the continuation of the trial. Unless the trial is permanently discontinued, PI, the research team, and IAVI will not be made aware of any unblinded results.

15. **Procedures to Minimize Risks**: All study procedures will be performed by [name]. and his designees. All vaccinations with electroporation will be performed only by individuals who have successfully completed Ichor’s formal training seminar. The seminar will be conducted by Ichor personnel and will require approximately 60-90 minutes to complete. Topics will include setup and operation of the equipment, procedures for administration of the DNA vaccine, troubleshooting, and device care and storage. Each participant must successfully complete at least three mock administration procedures in order to demonstrate competency.

No more than one volunteer per day will be enrolled for the first four volunteers to receive electroporation in each dose group. For these four volunteers, an additional telephone call to assess safety and adverse events will be made on the day following vaccination. If four vaccinations by electroporation have occurred without greater than moderate adverse events, the remainder of the group can be enrolled with no fixed interval between volunteers.

All intramuscular vaccinations will be given by skilled nursing staff or physicians using sterile technique. The phlebotomy procedures will be performed by skilled professionals using sterile technique. The site of each vaccination will be given in alternating upper arms. No more than 550 mL of blood will be taken from an individual over an 8-week period. If a female subject becomes pregnant during the course of the study she will be followed up through to the end of the pregnancy (either birth of the baby or termination of the pregnancy). If the pregnancy results in birth, a pediatrician will examine the baby approximately 2-4 weeks after birth.

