| Local and Systemic Reactogenicity Assessment (pre & post vaccination) |  | **X** | **X** | **X** | **X** | **X** | **X** | **X** | **X** | **X** | **X** |  |  | **X+** | **X+** | **X+** | **X+** | **X+** | **+** | **+** | |  | |
| Hep Bs Ag, Hep C ABS, Syphilis | **X** |  |  |  |  |  |  |  |  |  |  |  |  |  |  |  |  |  |  |  | |  | |
| Hematology and Clinical Chemistry | **X** | **X** |  |  | **X** | **X** | **X** |  |  | **X** | **X** | **X** | **X** | **X** |  |  | **X+** | **X+** |  | **X** | | **X** | |
| Anti-DS DNA |  | **X** |  |  |  |  |  |  |  |  |  | **X** |  |  |  |  |  | **X** |  | **X** | |  | |
| Urine dipstick | **X** | **X** |  |  | **X** | **X** | **X** |  |  | **X** | **X** | **X** | **X** | **X** |  |  | **X+** | **X+** | **X+** | **X** | | **X** | |
| Immunology (CD4/CD8) |  | **X** |  |  |  |  |  |  |  |  |  |  | **X** |  |  |  |  |  |  |  | | **X** | |
| PBMCs for Cellular immunogenicity assays (ELISPOT&CFC) and storage |  | **X** |  | **X** | **X** | **X** | **X** |  | **X** | **X** | **X** | **X** | **X** | **X** |  | **X+** | **X+** | **X+** | **X+** | **X** | | **X** | |
| Binding/ Neutralizing Antibody Responses |  | **X** |  | **X** | **X** | **X** | **X** |  | **X** | **X** | **X** | **X** | **X** | **X** |  | **X+** | **X+** | **X+** | **X+** | **X** | | **X** | |

ET = Early Termination

b Post-test counseling will be offered after HIV test results are available, at the next study visit or when available according to the site’s SOPs

** The first four subjects in each dose group who receive their vaccination by electroporation, an additional telephone call to assess safety and adverse events will be made on the day following the vaccination

**+**Vaccination on Week 36 and follow-up visits on Weeks 37, 38, 40 and 44 are optional, and apply only to those volunteers randomized to EP in the high dose cohort who elect to receive a third vaccination

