**APPENDIX C: ADVERSE EVENT SEVERITY ASSESSMENT TABLE**

| **PARAMETER** | **MILD** | **MODERATE** | | **SEVERE** | |
| --- | --- | --- | --- | --- | --- |
| **General Principle for Severity Assessment** | Mild discomfort. Minimal or no limitation of daily activity.  No need for medical intervention. | Moderate discomfort.  Some limitation of daily activities (e.g. able to work part-time)  May require minimal or no medical intervention | | Severe discomfort. Marked limitation of daily activities (e.g. unable to work). Requires medical intervention. | |
| **LOCAL REACTOGENICITY:** | | |  | |  |
| **Pain and tenderness** | Minimal discomfort associated with minimal or no limitation of use of arm | Moderate discomfort with some limitation of use of arm causing some interference with daily activities. May require single dose of analgesic or NSAID. | | Severe discomfort with significant limitation of use of arm causing marked limitation of daily activities (e.g. unable to work). Requires medical intervention (e.g. repeated doses of analgesic or NSAID). | |
| **Erythema (redness) or skin discoloration** | Light red blush up to 25% of the circumference of the upper arm | Marked redness involving up to 50% of the circumference of the arm | | Brick red involving >50% of the circumference of the upper arm | |
| **Edema (swelling)** | Light edema involving up to 25% of the circumference of the upper arm | Marked edema involving up to 50% of the circumference of the arm | | Significant edema >50% of the circumference of the upper arm | |
| **Induration** | Hardening under the skin <1.5 cm in diameter | Hardening under the skin 1.5-3.0 cm in diameter | | Hardening under the skin >3.0 cm in diameter | |
| **Skin damage (vesicle, ulcer)** | Vesicles or superficial disruption of epithelium < 1 cm | Vesicles or superficial disruption of epithelium 1-2 cm | | Full thickness disruption of the epithelium (ulceration) > 2 cm | |
| **Formation of crust, scab or scar** | Crust, scab or scar = 2cm | Crust, scab or scar 2­4cm | | Crust, scab or scar > 4cm | |

| **SYSTEMIC REACTOGENICITY** | |  |  |
| --- | --- | --- | --- |

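### A Grade 3 or higher injection reaction removes the volunteer from the study, and no available text keeps that volunteer in the remaining scheduled safety visits

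*Protocol*

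**What the plan says.** The rule stands in the list of risks (Protocol, Risks and Alternative Methods, item 5): "volunteers will be removed from the study if injection reactions ≥ Grade 3 in severity occur". Its object is the study, not the vaccination course.

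Other parts of the protocol bear on it:

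- The trial-level stopping rule is headed "Indications for discontinuation of vaccinations in all volunteers", so separate wording for stopping doses exists.
- In the Data and Safety Monitoring Plan, the paragraph on reporting serious adverse events sets the date of study completion. One example it gives is that "the participant is prematurely discontinued from the study". After completion it covers only serious adverse events reported spontaneously within 30 days.
- The adverse event definition requires that "The onset and end dates, severity and relationship to study vaccine and EP device will be recorded in the medical record for each event".
- Primary Endpoints lists "Severe other adverse events (including laboratory abnormalities") and all serious adverse events, alongside severe local reactions.
- The monitoring plan names Appendix C as the severity table. Its levels are mild, moderate and severe, without grade numbers. Severe induration is "Hardening under the skin >3.0 cm in diameter".
- Appendix A carries the legend "ET = Early Termination", but the table as extracted shows no such column.

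**The concern.** A severe injection reaction is a sound reason to withhold another dose. It is not a reason to stop observing the volunteer. Safety is the only primary objective, and two of the primary endpoints (other severe adverse events with laboratory abnormalities, and all serious adverse events) depend on visits and blood tests that run to Week 56.

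The loss is also selective, because a primary safety endpoint triggers it. Item 5 itself links greater plasmid uptake under electroporation to more frequent or more severe local reactions, and the text that follows raises integration risk on the same ground. The volunteers who leave may therefore be those in whom later safety matters most. Observed counts of later events can only equal or fall below the counts under continued follow-up. No analysis plan can recover visits that were not held.

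**Working it through.** **Reading the rule.** Three texts fit together: removal is from the study; premature discontinuation counts as completion; and only spontaneous reports of serious events within 30 days are covered after completion. Procedures to Minimize Risks does write in continued follow-up for pregnancy. Nothing comparable is written for a volunteer removed for a reaction.

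**Inputs for the count (Appendix A).** Post-dose clinic visits in the two-dose schedule are Weeks 1, 2, 4, 8, 9, 10, 12, 16, 24, 36, 48 and 56, which is 12. Haematology/chemistry is drawn at Weeks 2, 4, 8, 10, 12, 16, 24, 36, 48 and 56, which is 10. Post-dose anti-dsDNA tests fall at Weeks 16 and 48, which is 2. The optional third dose adds visits at Weeks 37, 38, 40 and 44 (12 + 4 = 16), laboratory tests at Weeks 38 and 40 (10 + 2 = 12) and anti-dsDNA at Week 40 (2 + 1 = 3).

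**Assumption.** Removal takes effect at the first clinic visit after the dose, so that visit is held and later ones are lost.

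**After dose 1 (removal at Week 1).** No second dose would follow even under the fix, so Week 8 (vaccination) and Weeks 9, 10 and 12 (post-second-dose checks) are set aside. That leaves Weeks 2, 4, 16, 24, 36, 48 and 56: 7 visits, each with haematology/chemistry. Keeping Week 8 as a check makes it 8 and 8.

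**After dose 2 (removal at Week 9).** Weeks 10, 12, 16, 24, 36, 48 and 56 are lost.

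**After the optional dose (removal at Week 37).** Visits at Weeks 38, 40, 44, 48 and 56 are lost, with laboratory tests at Weeks 38, 40, 48 and 56.

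| Removed after | Visits lost | Haematology/chemistry lost | Anti-dsDNA lost | Visits / laboratory tests lost, net of one Early Termination visit |
|---|---|---|---|---|
| Dose 1 | 7 (8 with Week 8) | 7 (8 with Week 8) | 2 of 2 | 6 / 6 (7 / 7) |
| Dose 2 | 7 of 12 | 7 of 10 | 2 of 2 | 6 / 6 |
| Optional dose | 5 of 16 | 4 of 12 | 2 of 3 | 4 / 3 |

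**Effect on precision, for scale only.** The protocol's zero-event upper bounds reproduce as 1 − 0.025^(1/n): 0.369, 0.206 and 0.142 for n = 8, 16 and 24, against 0.37, 0.21 and 0.14 stated. For events arising after removal, n shrinks. One volunteer lost from a dose group of 8 gives 1 − 0.025^(1/7) = 0.410. One lost from 24 gives 1 − 0.025^(1/23) = 0.148, and two lost give 0.154.

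**How often.** The protocol gives no rate of such reactions. At an assumed 2% to 20% per volunteer, expected removals among the 24 active electroporation recipients are 24 × 0.02 = 0.5 to 24 × 0.20 = 4.8. The chance of at least one is 1 − 0.98^24 = 38% to 1 − 0.80^24, above 99%.

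**The case against.** The strongest reply is that the sentence describes a risk and is not an operational withdrawal rule, and that only further vaccination was meant. Annual Reporting of AEs separates study drug discontinuation from premature discontinuation of the subject, so stopping the product in one person was foreseen. The trial-level heading is also weak evidence about wording for an individual. The text directly after Procedures to Minimize Risks was not available and could hold a withdrawal rule. All of this stands as doubt about intent. It does not alter what the available sentence says, and if only vaccination was meant, the same correction is needed.

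The safeguards are real. The DSMB reviews severe related reactions, and three or more volunteers with a related, clinically significant severe event suspend the trial. This limits how many could be removed before review, but it restores no visits for those already removed. The analysis is descriptive, so no confirmatory conclusion depends on the clause.

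A reader might go further in four ways that the documents do not support:

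- **That the severe local reaction rate is biased.** The triggering reaction and its severity are recorded, so it is not.
- **That 11 of 12 visits and 10 of 10 laboratory tests are lost after dose 1.** Those counts include Weeks 8, 9, 10 and 12, which serve a dose that would not be given.
- **That capture of serious events stops at removal.** Spontaneous reports within 30 days are still covered, though that window is short and passive.
- **That induration over 3.0 cm certainly triggers removal.** Appendix C has no grade numbers, and a threshold of Grade 3 or above suggests a scale with a higher level. Equating Grade 3 with severe is an inference.

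**Conclusion.** The point holds as a fault in trial conduct worth correcting. Followed as written, the clause ends scheduled safety follow-up in the most reactive volunteers, and later severe events, laboratory abnormalities and serious events in them can be missed.

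Per affected volunteer the loss is about half or more of the relevant remaining schedule after dose 1 or dose 2, including both post-dose anti-dsDNA tests, and about a third of visits and laboratory tests after the optional dose. Across the trial the size is unknown. The bounds for later events move little for the 24 pooled and more within a dose group of 8.

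This rests on four assumptions: Grade 3 means severe in Appendix C; removal occurs at the first clinic visit after the dose; the unavailable text holds no contrary rule; and any Early Termination visit is a single one, which would return one visit and one set of laboratory tests.

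**What to change.** Replace the clause in item 5 with: *Volunteers with a severe (Appendix C) injection reaction will receive no further vaccination but will continue scheduled safety follow-up to Week 56 unless they withdraw consent; visits tied only to a dose not given may be omitted.*

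In the Data and Safety Monitoring Plan, where the date of study completion is defined, add that stopping vaccination is not premature discontinuation from the study.

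The cost is a wording amendment. The retained visits and tests are already in Appendix A. The consent form was not available; if it repeats the clause, it should be aligned.

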**A Data and Safety Monitoring Board has been composed to oversee data and safety for the Rockefeller/ADARC site.**

## Standard Operating Procedures (SOPs) for the Data and Safety Monitoring Board (DSMB):

- The charter of the DSMB is to provide an ongoing assessment of volunteer safety during the ADVAX + EP Clinical Trial. The DSMB will consist of independent individuals who have no relationship to the Principal Investigator and Co-Investigators involved in the trial. No member of the DSMB will have any direct responsibility for the clinical care of trial volunteers. No representative of IAVI, Ichor or ADARC or their designees may be a member of the DSMB. However, the DSMB may invite the principal investigator (PI) or designee and an IAVI and/or ADARC representative to an open session of a DSMB meeting to provide information on study conduct, present data, or to respond to the members’ questions.
- The names, university affiliation and title, area of expertise, and contact information of each of the DSMB members are provided to the IRB (as listed above).
- All updated versions of the protocol and Investigator Brochure (I.B.) will be provided to the DSMB members.
- The DSMB will teleconference to review the trial data at least 14 days after both of the following criteria have occurred in the first group: after 12 volunteers in the first group have received their first vaccination *and* at least 8 volunteers in the same group have received both vaccinations. Similarly for group two, the DSMB will teleconference after 14 volunteers in the second group have received their first vaccination *and* at least 8 volunteers in the same group have received both vaccinations before proceeding to the next dose group. The DSMB must approve escalation to the next dose. At least two members are required to review the data before approval. Additional meetings will take place if there are indications for an interim review, which may be unblinded at the discretion of the DSMB.
- The study team will provide the DSMB with updated records of all adverse events (AEs) of a grade 2 or higher prior to each teleconference. The DSMB will be asked to review all severe clinical adverse/reactogenicity events judged by the Principal Investigator or designee to be possibly, probably or definitely related to vaccine.
- The DSMB will be asked to review on an interim basis all severe laboratory adverse events confirmed on retest and judged by the Principal Investigator or designee to be possibly, probably, or definitely related to vaccine.
- The DSMB will provide a written report to the PI after each teleconference and the PI in turn will distribute these reports to the study team, the sponsor, and the IRB.

